### Recruitment

The strategy to achieve adequate participant enrolment and the target sample size was to involve ten participating centers and extend the enrolment period to 3 years.

## Methods: assignment of interventions

### Allocation

All patients who consent to participate and meet the inclusion criteria will be randomized. Participants will be randomly assigned to either a control or experimental group with a 1:1 allocation in accordance with a computer-generated randomization schedule, stratified by participating center, using blocks of a fixed large size. The block size will not be disclosed to ensure concealment.

Randomization management is managed centrally by the REDCap Randomization Module software and is based on an allocation table created by the data analyst ([name]). The allocation table and the details about the restricted randomization (e.g., blocking size) are concealed in a separate document that is unavailable to trial implementers until the end of the study.

Each time a new patient is enrolled and entered in the database by the study coordinator of a center, REDCap will check the allocation table and assign that subject’s randomization field value, which will be derived from the next match in the table based upon the criteria (participating center).

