**Methods and analysis:**

This is a prospective, randomized, controlled study.

Patients will be randomized into two groups:

1. Group 2D: the preoperative workup for these patients will consist of a contrast-enhanced chest CT with two-dimensional (2D) reconstructions (axial, coronary, and sagittal);

2. Group 3D: the preoperative workup for these patients will consist of a contrast-enhanced chest CT with two-dimensional (2D) reconstructions (axial, coronary, and sagittal) and a 3D reconstruction (volume rendering) of the same chest CT employing dedicated software.

The primary endpoints will be negative margin (R0) resection rate, resection margin (staple line-to-tumor distance), and thoracotomy conversions.

We will use Fisher’s exact test for binary outcomes and Mann–Whitney *U* test for continuous outcomes. For subgroup analyses, we will use regression. Multivariable analyses will be based on logistic regression for binary outcomes and linear regression for continuous outcomes.

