### Study setting

#### Country selection

Ten international high-volume thoracic surgery departments currently participate in the study design. We have included three continents: Europe (Italy, Germany, Belgium), Asia (Hong Kong and Palestine), and the USA (Boston, MA). We selected centers with significant cultural differences to demonstrate the reproducibility of the proposed intervention.

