### Sample size

No data in the current literature was found about the other primary outcome margin- and disease-free resection. Therefore, the sample size was calculated based on the primary outcome conversions from minimally invasive to thoracotomy procedure.

To calculate sample size, we use data about conversion derived from previous literature [17–21]. The conversion rate for patients in the 2D group is estimated to be 9.4% [19]; the retrospective study has shown a reduction to 2.6%. Therefore, the required sample size to confirm superiority was 274, with a power of 80%, a one-sided significance level of 0.05, an accrual period of 3 years, and a follow-up period of 1 month. The planned total sample size was set at 288 patients to account for loss at follow-up.

Systematic methods such as reminders to contact patients, make appointments, and monitor retention will be employed to improve participant retention and will not expenses for follow-up visits and procedures.

We have used for the sample size determination the R software (package pwr) [26].

Two pre-specified interim analyses were conducted after the accrual of half of the planned patients and after accrual completion. To keep the study at a 5% one-sided significance level, we used the Lan–DeMets alpha-spending function [27] with an O’Brien–Fleming approach [28].

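### Randomization is stratified by center but the named tests (Fisher, Mann–Whitney) ignore center: a conservative mismatch whose size depends on between-center variation that the article does not give

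*Protocol article*

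**What the plan says.** The Allocation section describes a 1:1 computer-generated schedule "stratified by participating center, using blocks of a fixed large size". Center is the field on which REDCap matches each new patient to the allocation table. Under Country selection the authors write "We selected centers with significant cultural differences", and the sites mix university and hospital departments.

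The tests are named in the abstract, under Methods and analysis: Fisher's "exact test for binary outcomes" and Mann–Whitney for continuous outcomes. Multivariable logistic and linear regression are also planned there and under Statistical methods. Their covariates are not listed, and center is not mentioned in connection with any analysis.

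The Sample size section rests on conversion to thoracotomy: "The conversion rate for patients in the 2D group is estimated to be 9.4" percent, and "the retrospective study has shown a reduction to 2.6" percent. It concludes that "the required sample size to confirm superiority was 274, with a power of 80%, a one-sided significance level of 0.05", and then "The planned total sample size was set at 288 patients to account for loss at follow-up".

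**The concern.** When allocation is balanced within centers and the outcome differs between them, the treatment contrast is free of the between-center variance. An unstratified test still counts that variance in its null distribution. Its p-values are then too large, its actual error rate falls below nominal, and power is lost. The affected outcomes would include conversion and resection margin (both primary), operating time, blood loss and length of stay. With few conversions expected, even a modest loss counts. How much is lost depends on how far the centers differ.

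**Working it through.** **Inputs from the article.** Conversion 9.4% vs 2.6%; N 274, raised to 288 (144 per arm); 1:1 allocation; ten centers; one-sided 0.05 under Sample size but two-sided 0.05 under Statistical methods, so both are shown. Expected conversions: 144 × 0.094 + 144 × 0.026 = 13.5 + 3.7, about 17.

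**Assumptions, not in the article.** Center effects normal on the logit scale with SD 0, 0.5, 1.0 or 1.5; marginal rates held at 9.4% and 2.6%; centers equal (28–30 patients) or unequal (80 down to 6). For the continuous endpoint: ICC 0 to 0.3 and an effect of 0.33 total SD.

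**1. The stated sample size.** The article says "We have used for the sample size determination the R software (package pwr"), which uses the arcsine effect size. h = 2·asin(√0.094) − 2·asin(√0.026) = 0.2993. Per arm, n = 2 × ((1.645 + 0.842)/0.2993)² = 138.0, so 276–278 in total against the stated 274. Power at 274 is 79.7%. The figure reproduces closely and takes no account of center.

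**2. Unstratified tests, no center effect.** Exact binomial enumeration at 9.4% vs 2.6%:

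| | Fisher | Uncorrected chi-square |
|---|---|---|
| N = 274, one-sided | 70.1% | 80.7% |
| N = 274, two-sided | 57.7% | 68.4% |
| N = 288, one-sided | 72.6% | 80.9% |
| N = 288, two-sided | 60.7% | 70.4% |

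At 288 the gap is 80.9 − 72.6 = 8.3 points one-sided and 70.4 − 60.7 = 9.7 two-sided. Center plays no part in it.

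**3. Effect of center on conversion.** Simulated power at N = 288, equal centers, 10,000 trials per row, one-sided 0.05:

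| Center SD (logit) | Fisher | Exact test stratified by center | Chi-square | CMH by center |
|---|---|---|---|---|
| 0 | 73.0 | 73.2 | 81.0 | 81.3 |
| 0.5 | 72.2 | 72.9 | 80.7 | 81.4 |
| 1.0 | 70.1 | 72.2 | 80.1 | 81.3 |
| 1.5 | 70.0 | 73.6 | 80.9 | 82.4 |

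The cost of ignoring center is the difference between tests of the same kind. Exact tests: 0.2, 0.7, 2.1 and 3.6 points. Asymptotic tests: 0.3, 0.7, 1.2 and 1.5. Two-sided, the costs are 0.4, 0.9, 2.1 and 4.4 (exact) and 0.2, 0.8, 2.0 and 3.8 (asymptotic). Unequal centers give 0.2 to 3.6.

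**4. Type I error, common rate 6%, one-sided.** With no center effect, Fisher has 2.8% and chi-square 5.0%. At SD 1.0–1.5 with equal centers, chi-square falls only to about 4.6% and Fisher to 2.3–1.9%. Most of Fisher's conservatism is therefore discreteness, with a smaller part from center. CMH two-sided size was 4.7–5.0% in runs of 100,000 trials. In runs of 5,000 its one-sided size ranged from 4.5% to 6.2%, with a Monte Carlo standard error of √(0.05 × 0.95/5000) = 0.3 points.

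**5. Continuous endpoint, two-sided 0.05.** With 288/4 = 72 and the Wilcoxon efficiency 3/π, the standardized effect at ICC 0 is 0.33 × √(72 × 3/π) = 2.736. Balance within centers shrinks the true variance of the Mann–Whitney statistic by about (1 − ICC), while the test still assumes the full variance. So:

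- Mann–Whitney power ≈ Φ((2.736 − 1.96)/√(1 − ICC))
- Mann–Whitney size ≈ 2Φ(−1.96/√(1 − ICC))
- stratified power ≈ Φ(2.736/√(1 − ICC) − 1.96)

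| ICC | Mann–Whitney, formula | Stratified, formula | Mann–Whitney size, formula | Simulated, Mann–Whitney vs van Elteren |
|---|---|---|---|---|
| 0 | 78.1% | 78.1% | 5.0% | 78 vs 77 |
| 0.1 | 79.3% | 82.2% | 3.9% | 80 vs 81; 79 vs 81 |
| 0.2 | 80.7% | 86.4% | 2.8% | 81 vs 85; 81 vs 86 |
| 0.3 | 82.3% | 90.5% | 1.9% | 84 vs 90; 82 vs 89 |

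The simulated pairs come from two sets of runs, of 6,000 and 3,000 trials (ICC 0 in the first only). The formula slightly favors the stratified test because it ignores the small loss from ranking within centers of about 29 patients. In the larger set, van Elteren size was 4.5–5.0% throughout.

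**The case against.** **Attributing the whole conversion gap to center.** A reader who compares Fisher (61% two-sided) with CMH (71%) might infer that ignoring center costs about 10 points. The article's figures do not support this. The gap is there in full at center SD 0, an unstratified chi-square closes nearly all of it, and an exact test stratified by center closes almost none.

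**Center differences are not documented.** This stands. The article speaks of cultural differences, not outcome differences, and reports no center rates or ICC. It also says that no literature data were found for the margin outcome. Every center-related figure above is therefore conditional.

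**The named tests are still valid.** This also stands. Ignoring center makes them conservative, so the risk is a missed effect, not a false claim of benefit.

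**The unseen analysis plan may adjust for center.** It may do so in the multivariable models, whose covariates are not given, and nothing here shows that center is left out of them. But Fisher and Mann–Whitney are the tests the article names for the outcomes, and they cannot carry a center adjustment. A plan that used stratified tests would depart from the published text.

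**CMH has its own weakness.** It is asymptotic, with about 17 events over ten centers. On average 1.65 (SD 0) to 4.40 (SD 1.5) centers would have no event and so contribute nothing. That is fair, but its simulated size stayed near 5%.

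**Conclusion.** The point holds as a mismatch between a center-stratified design and unstratified named tests. The consequence is lost power, small for conversion and possibly larger for continuous endpoints. Attributable to center: about 0–2 points on conversion up to logit SD 1.0 and about 2–4 at SD 1.5; on a continuous endpoint with a 0.33 SD effect, about 0, 1–2, 4–5 and 6–7 points at ICC 0, 0.1, 0.2 and 0.3. These rest on assumed heterogeneity and, for the continuous endpoint, an assumed effect size.

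A separate loss of 8–10 points on conversion needs no assumption about centers. It follows from using Fisher's test with the article's own rates and 144 per arm, where power is about 73% one-sided or 61% two-sided against the 80% planned. It should be reported as the effect of Fisher's discreteness.

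**What to change.** State that the primary analysis is stratified by center:

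- conversion and other binary outcomes: CMH test with a Mantel–Haenszel risk difference or odds ratio;
- margin distance and other continuous outcomes: van Elteren test.

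For conversion, CMH deals with both losses, bringing power at N = 288 to about 81% one-sided or 71% two-sided. The two-sided figure is still below 80%, so the sidedness stated under Sample size and under Statistical methods has to be reconciled in any case. An exact test stratified by center would match the design but keep the discreteness loss (about 73% one-sided).

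The cost is wording, settled before outcomes are compared by arm. Center is already held in REDCap for randomization. If center turns out not to matter, van Elteren gives up about 1 power point. For CMH, the price is reliance on an asymptotic test with about 17 expected events.

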### Blinding (masking)

The trial participants will remain blinded to the group to which they belong to avoid any decision to withdraw from the trial. Even the pathologist does not know the assignment. The measures of outcomes are objective measures; this avoids ascertainment bias. However, outcome assessors and data analysts are kept blinded to the assignment. It is not possible to mask the assignment to the surgeons. This could induce a performance bias; it will be discussed in the limitations of the study.

### Data collection

The measures of outcomes will be collected by medical or nursing staff based on official patient records. Alerts will be sent via e-mail, marking the phases of entering the outcomes on the REDCap software concerning the intervention date. Any data upload delay of more than 2 months will be disclosed in the study. Primary outcomes are not allowed to be missing. The presence of the missing data will be communicated to both the coordinator of the participating center and the data managers. Reasons for missing data will be recorded.

Study data will be collected and managed using REDCap electronic data capture tools hosted at Regional Hospital, Bolzano, Italy [29, 30]. REDCap (Research Electronic Data Capture) is a secure, web-based software platform designed to support data capture for research studies, providing (1) an intuitive interface for validated data capture, (2) audit trails for tracking data manipulation and export procedures, (3) automated export procedures for seamless data downloads to standard statistical packages, and (4) procedures for data integration and interoperability with external sources.

Access to the study data will be restricted, and participating centers will only have access to their data. Incremental data back-ups will be performed daily.

Data collection takes place at regular intervals after surgery (1, 15, 30 days). Regular reminders will be sent to the coordinator of the participating center for operative and postoperative data to be entered in due course.

Participating centers are encouraged to enroll and randomize eligible patients no sooner than 30 days before the scheduled surgery date to minimize the number of ineligible patients after randomization or deviate from the intervention. Participants are retained in the group to which they were originally allocated (“as randomized” analysis). However, patients with missing data on primary outcomes will be excluded from the study. The patient exclusion will be recorded and made explicit in the results.

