### Statistical methods

We do not expect a relevant degree of missing data. Methods of multiple imputations (bagged trees imputation) will be used to calculate missing values.

Multivariable analyses will be based on logistic regression for binary outcomes and linear regression for continuous outcomes.

We will examine the residual to assess model assumptions and goodness-of-fit. *P*-values will be reported to three decimal places, with *p*-values less than 0.001 reported as *p* < 0.001. All analyses were performed using the R Statistical Software (4.2.2; R Core Team 2022). We will use 2-sided *p*-values with alpha ≤ 0.05 significance level for all tests.

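### Excluding randomised patients with missing primary-outcome data undermines the as-randomised analysis, is not reconciled with the imputation rule, and can discard observed conversions

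*Protocol article*

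**What the plan says.** Three statements bear on missing primary outcomes.

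- Data collection sets a target: "Primary outcomes are not allowed to be missing".
- The same section gives the analysis population. "Participants are retained in the group to which they were originally allocated", and the next sentence makes an exception: "patients with missing data on primary outcomes will be excluded from the study". Exclusions are to be recorded and reported.
- Statistical methods says "We do not expect a relevant degree of missing data" and continues: "Methods of multiple imputations (bagged trees imputation) will be used to calculate missing values". It does not say which variables this covers.

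More than one outcome is primary. The abstract states: "The primary endpoints will be negative margin (R0) resection rate, resection margin (staple line-to-tumor distance), and thoracotomy conversions". The Outcomes section lists the disease-free margin and conversion to thoracotomy. The Sample size section rests on conversion alone.

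**The concern.** The exclusion is from the study, not from the analysis of the variable that is missing. The text does not say whether one missing primary outcome is enough, but that is the natural reading. A patient with an observed conversion status and no margin value would then drop out of the conversion comparison, although nothing about conversion is missing.

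Two things are at stake. First, patients would be removed for a reason that arises after randomisation, so the conversion analysis would no longer cover everyone randomised whose conversion status is known. Second, the same missing margin is excluded under one section and imputed under the other, and the article does not say which rule governs. With about 17 conversions expected in the whole trial, losing a few matters if the loss is related to conversion.

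**Working it through.** **Inputs from the Sample size section.** "The conversion rate for patients in the 2D group is estimated to be 9.4" per cent, and "the retrospective study has shown a reduction to 2.6" per cent. One-sided alpha is 0.05, power 80%, 274 patients required and 288 planned. Allocation is 1:1 (Trial design), so 144 per arm. The test for binary outcomes is Fisher's exact test (abstract).

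**The plan's own figure.** The arcsine effect size used by the pwr package is h = 2·asin(√0.094) − 2·asin(√0.026) = 0.2993. Then n per arm = 2(1.645 + 0.842)²/h² = 138.0, or 276 to 278 in total. This is close to the stated 274. At 144 per arm the same formula gives 81.5% power. Exact enumeration of Fisher's one-sided test gives 73%. That gap comes from the choice of test and is a separate matter.

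**Loss unrelated to conversion.** The allowance is 288 − 274 = 14 patients, or 14/288 = 4.9%. With 5% lost from each arm (about 137 left), the rates stay at 9.4% and 2.6%. Arcsine power is 79.7%, so the cost is small.

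**Loss related to conversion, equal share in both arms (assumption).** The article gives no rate, so a range is shown. If a share q of converted patients is excluded and nobody else is, a true rate p is observed as p(1 − q)/(1 − pq). Expected conversions analysed are 144 × (0.094 + 0.026) × (1 − q).

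| q | Conversions analysed | Observed rates, 2D vs 3D | Risk difference (points) | Odds ratio | Fisher power, one-sided, 144 per arm |
|---|---|---|---|---|---|
| 0 | 17.3 | 9.4% vs 2.6% | 6.8 | 3.89 | 73% |
| 10% | 15.6 | 8.5% vs 2.3% | 6.2 | 3.89 | 68% |
| 25% | 13.0 | 7.2% vs 2.0% | 5.3 | 3.89 | 59% |
| 50% | 8.6 | 4.9% vs 1.3% | 3.6 | 3.89 | 40% |

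Reducing the arm sizes for the excluded patients barely changes power (68, 60 and 40%). The arcsine formula shows the same direction: 81.5% falls to 78, 71 and 57%. The odds ratio is constant because each arm's odds, p/(1 − p), are multiplied by the same 1 − q.

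**Loss related to conversion, unequal by arm (assumption).** If 25% of conversions are dropped in one arm only:

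- 2D arm only: observed rates 7.2% vs 2.6%, difference 4.6 points, arcsine power 58%.
- 3D arm only: observed rates 9.4% vs 2.0%, difference 7.4 points, apparent arcsine power 90%.

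Now suppose there is no true difference (9.4% in both arms) and only 3D-arm conversions are dropped. At 25% or 50% dropped, the observed 3D rate is 7.2% or 4.9%. One-sided Fisher rejection at 144 per arm is then about 12% or 34%, against 3% with no exclusion.

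**The case against.** **The mechanism is not documented.** A reader might infer that the rule selectively removes converted patients. The article does not say so. Conversion changes the surgical access, but the patient is still resected, and the eligibility criteria require NSCLC proven on the resected specimen, so a margin can be measured after conversion. This stands: the link between a missing margin and conversion is an assumption, and its size cannot be derived.

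**Little missingness is expected.** The article sets up alerts, escalation to coordinators and data managers, and recorded reasons. At q = 10%, fewer than two patients are lost (144 × 0.12 × 0.10 = 1.7). This also stands, and it makes the 25% and 50% rows stress cases rather than forecasts.

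**Bias toward zero.** A reader might infer that the effect is always diluted. That holds only for the risk difference with equal shares dropped. The odds ratio, which goes naturally with the planned logistic regression, does not move, and with equal shares two equal rates stay equal. With unequal shares the bias can go either way. Surgeons are unmasked (Blinding), so equal shares cannot be taken for granted.

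**No flat contradiction.** The as-randomised sentence governs group membership, and the exclusion is openly introduced as an exception to it, with reporting. The imputation sentence might be meant only for secondary outcomes and covariates. The first part stands: the exception undermines the as-randomised analysis rather than contradicting it outright. The second is a possible reading that the text does not state, so the sections remain unreconciled. Reporting an exclusion discloses it but does not repair it.

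**Bagged trees.** A reader might infer that the named method yields a single deterministic fill-in and so understates standard errors. The article speaks of multiple imputation and gives no implementation, so nothing in it supports that inference.

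**Conclusion.** The point holds as a badly fixed rule, not as demonstrated bias. What is certain from the text is that randomised patients with missing primary-outcome data leave the study, and that the imputation sentence makes no exception for them. On the natural reading, an observed conversion status is discarded because a different outcome is missing.

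The damage is conditional. It is minor if missingness is unrelated to conversion. If it is related, and equal in both arms, 10 to 50% loss among converted patients takes Fisher power from 73% to between 68% and 40%. If it is confined to one arm, the effect can be understated or overstated, and one-sided type I error could reach about 12% or 34% in the 3D-only cases shown. These figures rest on the planning rates, 144 per arm, no loss among unconverted patients, and assumed missingness shares that the article does not supply.

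The rule deserves correction even if missingness proves low: it governs the population for the outcome that sized the trial, and discarding an observed conversion status brings no benefit.

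**What to change.** 1. In Data collection, delete the sentence excluding patients with missing primary outcomes.
2. State that conversion is analysed in all randomised patients with known conversion status, in their allocated group, whether or not a margin is available.
3. Confine the handling of missing margins to the margin analyses.
4. In Statistical methods, state that multiple imputation applies to those margin analyses, with complete cases as a sensitivity analysis.

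The cost is a few sentences and slightly more programming. No new data are needed.
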